## Abstract

**Background:**

Acute psychiatric wards in Germany are often locked due to the assumption that opening could endanger patients and society. On the contrary, some findings suggest that aversive events such as absconding and attempted suicides do not occur more often on wards with an open-door policy. However, these data are probably biased with regard to differing patient populations on open and locked wards. To our best knowledge, the present study is the first prospective controlled study with a quasi-experimental design dealing with this issue.

**Methods:**

This study investigates whether indicators of an open-door policy, as measured by a priori determined outcomes, can be improved by a defined complex intervention on two intervention wards in two psychiatric hospitals, compared to two control wards with otherwise very similar conditions. Both hospitals contain two wards identical in structure and patient admittance policies, so that a similar study protocol can be followed with similar patient populations. Both hospitals have a defined catchment area and receive voluntary and involuntary admissions. In a baseline phase, wards will be opened facultatively (i.e., if it seems possible to staff). In the following intervention period, one ward per hospital will establish an enhanced open-door policy by applying additional strategic and personnel support. As a control group, the control ward will continue to be opened facultatively. After one year, control wards will be opened according to the open-door policy as well. Interventions will include the continuous identification of patients at risk as well as the development of individual care concepts and additional staffing. For this purpose, nursing and medical staff will be methodically supported on an ongoing basis by study staff.

Outcomes variables will be the percentage of door opening on each ward between 8 a.m. and 8 p.m., the percentage of all treatment days with the door opened and the number of involuntary treatment days with open doors. Data on frequencies of aggressive incidents, absconding, police searches, and seclusion or restraint will be used as control variables. Additional costs will be calculated.

**Discussion:**

Treating mentally ill patients on locked wards is a highly relevant and critically discussed topic. In particular, it is controversially discussed whether changes in door policy can be established without increasing risks to patients and others. This study aims to gain robust data on this issue, going beyond beliefs and questionable retrospective observational studies.

**Trial registration:**

Our trial “Open Doors By Fair Means” is retrospectively registered with DRKS (DRKS00015154) on Sept. 10th 2018 and displayed on the public web site. It is searchable via its Meta-registry (http://apps.who.int/trialsearch/).

## Background

In contrast to somatic hospitals, psychiatric clinics are authorized by public and civil law to restrain the patient’s freedom under defined conditions against their will. This involuntary commitment is justified by danger to the patient themselves or others, in Germany as well as in all other developed countries. In the short term this is possible depending on federal state law, e.g. for 24–48 h; in the longer term, the request of the clinic or a legal guardian by judicial authorization is required [1]. Traditionally, involuntary detention is ensured by locking the ward door, in severe cases accompanied by other restrictions such as seclusion or mechanical restraint.

Only about 10% of patients treated in German psychiatric hospitals are held against their will in the clinic [2]. Hence, the treatment of the remaining voluntary 90% of the patients behind locked doors, even if they are allowed to leave the ward at any time, raises ethical questions, such as whether this encroachment on fundamental rights is appropriate and necessary in the treatment of psychiatric patients [3, 4]. Austria has already adopted legislation to address these concerns. Voluntary patients do not need to be treated on locked wards unless they specifically request such conditions (which they usually do not). As a result, in most parts of Austria, psychiatric wards follow an open-door policy which is generally accepted by the public, courts, and the police. In a comparative study on differences between the Weissenau Hospital for Psychiatry in Germany, and the psychiatric hospital in Vienna, Austria, no significant differences were found regarding the frequency of absconding, police searches, suicide attempts, and mechanical restraint within the subgroup of involuntarily treated patients [5].

Since 2015, it is legally possible to treat involuntarily committed patients on open wards in some federal states of Germany [5, 6]. On the background of a movement claiming to abolish all coercive measures in psychiatric hospitals, the practice of locked acute psychiatric care units is a topic of intense discussion in Germany [4, 7]. In order to enable open-ward management, different strategies exist. A relationship-oriented approach with more intensive care for ‘difficult’ patients is preferred. In addition, architectural features such as the location of the nurses’ station, the presence of a counter or at least the presence of a nurse near the door, and the possibility of remote door locking are considered vital. The most extreme strategy is to mechanically restrain or seclude those patients who are at risk of leaving an open ward against medical advice. However, even if this seems to happen in some cases in Austria under conditions of generally open wards and maybe also in German hospitals with a strict open-door policy, most experts would consider such procedure as ethically dubious, if not unlawful [8]. Across Germany, there are considerable differences in hospital organization in terms of specialized wards, concentration or distribution of involuntary patients and so-called “intensive care units” (mostly not available). The most recent guideline of the German Association for Psychiatry and Psychotherapy on the prevention of coercive measures [9] does not express a clear recommendation regarding open wards or hospital organization due to a lack of robust evidence, but generally recommends a policy of least possible restrictions of all kinds. Some German clinics already claim to provide only wards with open doors [10].

Patients admitted or transferred to closed wards usually suffer from severe psychotic or manic symptoms. Others, in a smaller number, are either suicidal in the face of a depressive disorder or show self-harming behaviors. In both cases, restrictive interventions potentially might reinforce existing symptoms such as regressive tendencies or exacerbation of psychotic symptoms due to fear and loss of control [11–13].

50–85% of all suicides occur while patients take approved leave from the psychiatric unit. In most of these cases, patients suffer from affective or substance-related disorders. The concerns about this suicide risk and subsequent judicial liability are a major reason for keeping psychiatric wards locked [11, 14, 15].

However, the suspected risk of absconding seems to increase the probability of absconding: 58% of patients who escape or do not return from a leave name the locked door as one of the reasons [16–19]. Significantly fewer patients absconded or were discharged against medical advice during one year of open ward management in a study in the Department of Psychiatry, University of Basel, Switzerland [20]. Moreover, with the door open, compliance increased and the likelihood of self-harming behaviors, aggression, and refusal of medical treatment decreased.

So far, in contrast to intense discussions among professionals, there is little empirical work on the subject, with mostly retrospective observational data lacking adequate controls. For example, the impact of a change of door policy on coercive measures was investigated over a two-year period in a clinic-wide study in Basel, Switzerland. As a result, no increase in coercive measures on other wards was found and the frequency of coercive measures on the newly opened wards decreased overall [21]. However, there was a redistribution of involuntary patients to the remaining locked wards. In another study, two consecutive periods of six months in one acute care unit, one closed and one mostly open, were compared [22]. While patients did not differ in terms of gender, diagnosis, age and duration of treatment, violent incidents and coercive medication application occurred significantly more frequently during the closed-door period. Moreover, while the ward was open, absconding did not occur more frequently.

In a 15-year observational study, outcomes in 21 German psychiatric hospitals were examined retrospectively [23, 24]. Hospitals were dichotomized into those practicing an “open-ward policy” and those with a “locked-door policy”, defined by expert consensus. The probability of completed suicides was defined as the primary outcome measure for one paper [23], aggression, violence, and coercive interventions for the other [24]. Suicide attempts during treatment and absconding with and without return were defined as secondary outcome measures. In addition, differences between ward types regarding outcomes were examined. As a result, no statistically significant differences were found between hospitals regarding suicides and attempted suicides. Absconding with return occurred more often in hospitals with open-ward policy, whereas absconding without return occurred less frequently. Violence did not differ significantly between hospital types (“open door policy” and “locked door policy”), seclusion and restraint were reported less frequently in hospitals with “open door policy” [24]. All kinds of adverse events occurred less frequent on open wards compared to closed wards. The authors concluded that open wards have a positive effect on reducing aggression.

Although this dataset from 21 German clinics represents the largest database on the issue of an open-door policy and the two papers are often cited by those promoting a strict open-door policy, the study approach was subjected to strong criticism in terms of considerable flaws in design and methods [25]. Data was recorded over a long period of time for other purposes. Calculations were based on a simple division into clinics with a locked or open-door policy which was done retrospectively by the study authors based on personal knowledge. Neither the extent to which doors were actually open over the study period, nor whether they were open or closed during the adverse events nor which other interventions had taken place to avoid suicides, violence, or coercive interventions. Therefore causal interpretations are impossible. Moreover, the finding that violent incidences occur less often on open wards and similar findings relating to suicide attempts and the use of seclusion and restraint might easily be explained by the clinical practice to place patients considered at risk on locked wards, i.e., a serious sample bias. However, psychiatric inpatient treatment is not only about avoiding risks. It also focuses on therapeutic setting and ward atmosphere, which are crucial to its success. These include therapeutic hold as a precondition for therapy commitment, and also the support of the patients among each other [26–28]. To investigate the effects of an open-door policy on ward atmosphere from the nursing staff’s point of view, the parameters “safety”, “therapeutic hold”, and “patient cohesion” as well as the global atmosphere on closed wards, open wards and newly opened wards were measured in a study from a university psychiatric hospital in Switzerland via a questionnaire [23]. The global ward atmosphere was reported to be significantly better on newly opened wards than on closed or open wards. Also, the overall feeling of safety was reported to be above average on newly opened wards compared to closed or open wards. The authors attribute this to the establishment of new procedures for dealing with high-risk patients. This might be a specific measure that goes beyond the effect of door-opening and possibly provides an explanation for the significant difference between newly opened and already open wards. While no significant differences in terms of therapeutic hold were found, patient cohesion at newly opened wards was rated above average. The authors attribute this to the approach of “shared decision making”, which is expected to strengthen patients´ personal responsibility and might lead to a more caring behavior within the patient group. Overall, the authors conclude that it is possible to open closed wards without a higher safety risk and, moreover, that it is suitable for the implementation of a more supportive treatment environment.

Overall, structural conditions and traditions seem to account for the treatment of psychiatric patients behind locked doors. As of today, there are no controlled trials and no comparable populations to underpin the ongoing discussions, which are characterized by ideology and criticism of the current handling of coercive measures.

Therefore, the current study investigates whether an open-door policy can be established and which interventions can be used to care for special patients. We will collect quantitative data on duration of open door intervals, days with open doors and involuntary treatment days, adverse events and additional cost. Moreover, we will collect qualitative data from staff and patients on ward atmosphere, sense of security and general concerns on the open door management as well as qualitative data on the reasons for closing an open ward intermittently. In the course of the ongoing trend towards the opening up of psychiatric hospitals in order to create the least restrictive treatment atmosphere, well-made studies producing reliable numbers are urgently needed. Based on the findings of this study, we want to derive recommendations that can make a substantial contribution to new guidelines. These should facilitate decisions in dealing with difficult patients, to apply the least restrictive measures and provide security with regard to legal uncertainties.

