### Study participants

Data of all patients who are admitted to the acute wards of the University Department of Psychiatry and Psychotherapy Tuebingen and the Department for Psychiatry Friedrichshafen (part of the Clinic for Psychiatry and Psychotherapy I of Ulm University), between June 1st 2017 and March 31st 2020 will be collected. There is no specific target age group, but as only adults are treated at the participating wards, all patients will be over the age of 18. The 34 months of data collection include a four-month baseline phase, three months of implementation phase and a total of 27 months of intervention in the intervention wards. The investigation group is defined as those patients treated at the two intervention wards within the first 12-month period. The control group is defined as those patients treated at the other wards without specific interventions during the same period. To control for bias, we will compare distributions of diagnoses and how many patients are admitted involuntarily. In Tuebingen, we will also collect data on how long patients are allowed to leave the ward. In Friedrichshafen, there is no further differentiation, patients are either allowed to leave the ward or they are not. This represents different clinical practices which could not completely be harmonized. Furthermore, the number of patients and staff per day will be recorded.

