### Outcome measures

The primary outcome measures will be the average opening time of the four acute wards between 8 a.m. and 8 p.m. in percent, the percentage of treatment days with the door open (at least part time), as well as the number of involuntary treatment days with the door open. The latter means that if the door is open for one full day x and seven involuntary patients are present, this will count as 7 involuntary treatment days with open doors.

As secondary outcomes, the frequency of coercive measures (seclusion, restraint, involuntary medication), suicides, suicide attempts, severe self harm and aggressive incidents will be recorded as well as the frequency of absconding. This includes deviations from agreements in voluntarily treated patients, as well as searches for missing patients by the police. In Friedrichshafen, aggressive incidents will be documented with the Staff Observation Aggression Scale [29], in Tuebingen, the documentation of aggressive incidents is part of the survey which is to be filled out on a daily basis. Coercive measures will be routinely documented at both locations by a case register according to the law on assistance for persons with mental diseases in Baden-Wuerttemberg [2]. In addition, costs of the intervention per day with the door open are to be documented. Ward atmosphere will be assessed by staff and patients every six months by the Ward Atmosphere Scale [30].

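### The third primary outcome is a raw count that rises with more or longer detention at unchanged door opening, and no secondary outcome would show that rise

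*Protocol article*

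**What the plan says.** The Background of the protocol article treats detention as a restriction of liberty: "psychiatric clinics are authorized by public and civil law to restrain the patient’s freedom under defined conditions against their will". Commitment has to be justified by danger to the patient or others, and "in the longer term, the request of the clinic or a legal guardian by judicial authorization is required".

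Outcome measures names three primary outcomes: the percentage of time the door is open between 8 a.m. and 8 p.m., "the percentage of treatment days with the door open (at least part time", and the involuntary-day count, "as well as the number of involuntary treatment days with the door open". The worked example for the last one scores a fully open day with seven involuntary patients on the ward as 7. The abstract presents the outcomes as indicators that the intervention is meant to improve, so a higher value reads as better.

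The coercion outcome is "the frequency of coercive measures (seclusion, restraint, involuntary medication". The other clinical events counted are suicide, attempted suicide, severe self-harm, aggression, absconding and police searches. The abstract's control variables do not include detention either.

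Under Study participants, diagnoses and "how many patients are admitted involuntarily" are compared to control for bias. Data collection and management includes legal status in the daily door-status record, and the end of the Background names involuntary treatment days among the data to be collected. The same paragraph of the Background says that the results should help "to apply the least restrictive measures and provide security with regard to legal uncertainties".

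**The concern.** Legal status enters the outcomes in one place only, as the counting unit of the third primary outcome. That count is the product of how often the door is open and how many detained patients are present. A ward can raise it by opening the door more, which is the intended effect. It can also rise because more patients are detained, or are detained for longer, which is more restriction.

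The planned outcomes cannot separate the two. Detention is not in the coercion list. The admission comparison looks at status on entry, so it would miss a change from voluntary to involuntary during the stay, or a longer detention. It would also read any excess as case mix rather than as a possible effect of the policy.

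What is at stake is the conclusion about least restrictive care. If detention did rise on the intervention wards, the report could show more open-door involuntary days and no increase in coercion, and nothing in the planned outcomes would prompt a second look.

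**Working it through.** **The plan's own figure.** Third outcome = sum over open days of the involuntary patients present. One open day × 7 patients = 7, as the protocol states. With one more detained patient on that same day the outcome is 8, and 8/7 = 1.14. The door was open equally long, and the score is 14% higher.

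**Inputs for a general check.**
- Involuntary share s. The Background gives a national figure: "Only about 10% of patients treated in German psychiatric hospitals are held against their will in the clinic". The share on the study wards is not given, so 5% to 30% is assumed as a range.
- Fraction c of voluntary patients who become involuntary, applied to treatment days. The documents give no value; 2%, 5% and 10% are assumed.
- Door opening and occupancy are held fixed, to isolate the effect of legal status.

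**Formula.** The new involuntary share is s + (1 − s)c. The ratio of the new count to the old is [s + (1 − s)c] / s.

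**Results at s = 10%.**

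| c | New share | Ratio | Rise in third outcome |
|---|---|---|---|
| 2% | 0.10 + 0.90 × 0.02 = 0.118 | 1.18 | 18% |
| 5% | 0.10 + 0.90 × 0.05 = 0.145 | 1.45 | 45% |
| 10% | 0.10 + 0.90 × 0.10 = 0.190 | 1.90 | 90% |

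Over the whole assumed range, the smallest rise is at s = 30%, c = 2% (0.314/0.30 = 1.047, about 5%). The largest is at s = 5%, c = 10% (0.145/0.05 = 2.90, or 190%).

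**Would a denominator be enough?** Take 1,000 treatment days, 60% of them with the door open (assumed), s = 10% and c = 5%.

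| | No conversion | 5% converted |
|---|---|---|
| Treatment days with open door | 60% | 60% |
| Involuntary days | 100 | 145 |
| Involuntary days with open door (third outcome) | 60 | 87 |
| Open share of involuntary days | 60/100 = 60% | 87/145 = 60% |
| Involuntary days per 100 treatment days | 10.0 | 14.5 |

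Taking a share removes the false gain but still shows no change. Only the last row reveals the extra detention, so both pieces are needed.

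**Masking.** In the same example, door opening on involuntary days could fall by 1 − 0.10/0.145 = 31% before the raw count dropped below its old value.

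**The case against.** The strongest reply is that the substitution is hypothetical. Commitment requires danger and, in the longer term, a court's authorization; a clinic's request is not a clinic's decision. The Background says voluntary patients behind a locked door may be free to leave at any time, so it does not present the door as what holds them. The Interventions section allows the door to be closed at any time if a patient at risk wants to leave and other measures fail. That fallback would lower the opening-time outcome, and it makes resort to detention less likely. The substitution the authors themselves discuss, restraint or seclusion in place of a locked door, is measured. All of this stands. A reader might infer that open wards turn voluntary patients into involuntary ones; no passage says so, and the studies the Background cites on open doors mostly report favourable results on other events.

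A reader might also infer that legal status is ignored or that the whole primary result would be flattered. Neither holds. Legal status is documented, involuntary days are named as collected, and a rise in involuntary admissions would be visible in the bias check. Two of the three primary outcomes do not depend on legal status at all.

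Finally, the sizes are chosen rather than observed, the 10% is a national figure for all psychiatric hospitals, and all analyses are exploratory. That is also right, and it limits the weight of the point. It does not remove the point: the direction of the effect follows from the outcome definition alone, and the choice of outcomes is made in this document rather than left to an analysis plan.

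**Conclusion.** The point holds as a conditional blind spot. At fixed door opening, any increase in the number or length of detentions raises the third primary outcome and appears in no secondary outcome. The rise is 18% to 90% for conversion of 2% to 10% of voluntary patients at a 10% involuntary share, and about 5% to 190% over shares of 5% to 30%. These sizes rest on assumed shares and conversion fractions with door opening and occupancy held constant; only the direction comes from the protocol. The documents do not show, and this point does not claim, that the policy increases detention. It is a cheap improvement that would allow the trial to say whether opening the door lessened restriction or changed its form.

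**What to change.** In Outcome measures:

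1. Express the third primary outcome as the share of involuntary treatment days with the door open (involuntary days with open door / all involuntary days). The raw count can be kept as a descriptive figure.
2. Add to the secondary coercion outcomes: involuntary treatment days per 100 treatment days, by ward and period, compared between intervention and control wards. State that the third primary outcome is read together with it.
3. Where the records give legal status over the stay, also report changes from voluntary to involuntary status per 100 voluntary admissions.

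The cost is one or two more exploratory comparisons. The third outcome already needs a count of detained patients on open days; legal status must now be tabulated for closed days as well. Door policy and clinical procedures on the wards are unaffected.
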